**PROPOSED STARTING DATE: Nov 2003 DURATION: 2 years**

**1) SUMMARY**

Pregnant women are vulnerable to malaria, with significant implications both for their health and for the pregnancy. Sulfadoxine-pyrimethamine (SP) is currently the first line drug for the treatment of malaria in pregnancy in Tanzania and surrounding countries, but resistance is emerging rapidly. Alternative drugs must be found, and new drugs and drug combinations are being recommended by many for deployment as first line treatment at the point that SP resistance forces a policy change. However, there are few data on the safety and efficacy of these combinations in pregnant women. This randomised trial aims to assess efficacy and safety, including birth outcome, in pregnant women with malaria in the second or third trimesters. A total of 900 pregnant women will be randomised either to standard treatment (SP) or to one of three potential drugs, or drug combinations recently recommended by a WHO expert panel. These will be SP-amodiaquine, chlorproguanil-dapsone (Lapdap), and amodiaquine-artesunate. Primary outcome will be treatment failure at day 28. Secondary outcomes will include maternal side effects, foetal viability and birth outcome.

## 2). Background.

Malaria in pregnancy is an important preventable cause of maternal and perinatal morbidity and mortality (Brabin 1991). In areas where infection with *Plasmodium falciparum* is endemic, immunity to malaria develops over the first few years of life, and older children and adults rarely suffer severe complications of infection. An exception is during pregnancy, when risks of severe maternal anaemia (Shulman 1996) and low-birthweight (Steketee 1996a) are increased by malaria infection. The risks are greatest in the first pregnancy and decrease with increasing gravidity (McGregor 1984). Malaria infection in pregnancy in these situations is often asymptomatic (Steketee 1996b). For this reason, preventative strategies such as chemoprophylaxis or intermittent treatment with antimalarials have been recommended in pregnancy (WHO). It is also now recommended that case management of severe anaemia includes antimalarials.

However, all pregnant women are also at increased risk of clinical disease compared with non-pregnant women (Diagne 1997). Clinical disease during pregnancy needs prompt effective treatment, as even seemingly uncomplicated disease can result in foetal loss and can progress to severe disease. Particular dangers of severe malaria in pregnancy (which are more common and more severe in non-immune women and possibly women with HIV infection), include high fever, which can precipitate a premature delivery, hypoglycaemia, severe anaemia, pulmonary oedema and maternal death (Meek 1988, Nosten 1991). Severe anaemia is a particular problem in pregnant women in Africa who were, before pregnancy, semi-immune.

In Tanzania, current first line treatment for all patients with uncomplicated malaria is sulfadoxine-pyrimethamine (SP). This has the advantage of being a one-dose treatment that can be given as an outpatient. The only current alternative treatment for pregnant women is quinine which needs to be given for 7 days, and usually therefore requires in-patient treatment. Quinine is also often associated with unpleasant side effects. For many women without severe disease, outpatient management with an effective antimalarial should suffice. However, there is an urgent need to find an effective alternative to SP due to increasing levels of resistance.

*Drug resistance:* Increasing chloroquine resistance has necessitated changing the first line antimalarial drug to sulfadoxine/pyrimethamine (SP) in many countries in Africa. Emerging resistance to SP is increasing at an alarming rate. Drug sensitivity tests conducted recently by the East Africa Network for Monitoring Antimalarial Treatment (EANMAT) have shown SP-treatment failure rates of  $\geq 25\%$  at several sites (EANMAT, 2001a), the threshold level of drug resistance recommended by the WHO for changing an antimalarial drug. Nonetheless, options of alternative drugs are limited because the few available drugs are either not recommended for use as monotherapy (artemisinins), are expensive (mefloquine, Malarone), have inappropriate dosage schedule for outpatient use (quinine), or have an uncertain safety profile in pregnancy.

*Drug resistance within the study area:* The study will be done in Muheza district, where there is already considerably expertise in running clinical trials successfully under the direction of [name], currently seconded to the Gates malaria programme from NIMR. Muheza district participated in the study on “Malaria chemosuppression during pregnancy” by [name] *et al.* (1993) and the LSHTM has long-standing research links in this area. The lowlands of Muheza district experience hyperendemic to holoendemic malaria (Clyde 1967; MARAMAP 2000). More than 95% of the malaria infections are caused by *Plasmodium falciparum*. Resistance of *P. falciparum* to SP is relatively high in the district, providing a strong rationale for using this site to test new combinations that might be adopted nationally. In a recent study in Muheza, the 14-day parasite clearance by SP was 55% ([name] *et al* 2001). In this study, re-treating malaria clinical episodes emanating from parasitaemia that failed first treatment with SP resulted in higher SP-resistance (61%). In contrast, a 3-day course of chlorproguanil-dapsone (LapDap) cleared all but 7% of the parasitaemia. EANMAT data from Mkuzi Health Centre

[name] et al. Protocol Final (v 2.1 Nov 2003, with modification Oct 2004) (Muheza district), showed that the combined early and late treatment failure rate to amodiaquine was 11% (7/64) compared to 34% (23/68) for SP (EANMAT, 2001b). Malaria parasites in this area are still highly sensitive to quinine, which is used as the third line drug or for treating severe and complicated malaria. Quinine therapy either alone for 7 days or as a 3-day course plus a single curative dose of SP cleared parasitaemia by day 7 in all patients (n=200) admitted to Muheza Hospital in 1997/98 with severe and complicated malaria ([name] *et al-in preparation*).

*Existing treatment policy:* The National malaria treatment policy until August 2001 was to use chloroquine to treat and prevent malaria in pregnant women attending Maternal and Child Health (MCH) clinics. The new policy, operational since 1st September 2001, is to use SP for first line treatment of malaria and for Intermittent Preventive Therapy (IPT) in pregnant women. There is high SP-resistance in the district ([name] *et al* 2001) although published data is from studies in children, so cannot be automatically extrapolated to pregnant women. HIV seroprevalence among blood donors is 11% in Muheza district (Acting Medical Superintendent of the hospital-*personal communication* 2002), although blood-donor seroprevalence tends to overestimate population seroprevalence in East Africa. HIV is a co-infection shown to impair the efficacy of IPT with SP during pregnancy. For these reasons the current use of SP alone during pregnancy is questionable.

The health leadership for Muheza district and Tanga region recognizes the threat posed by malaria, in particular antimalarial drug resistance and the urgent need to search for and institute practicable control measures for malaria during pregnancy. The Medical Superintendent for Muheza Designated District Hospital (DDH) and the Regional Medical Officer for Tanga region agree with the aims of this study and believe that it will help to develop an evidence based treatment policy.

*The trial and its justification.* Recently, WHO proposed four different drug regimes for treating uncomplicated malaria. A number of trials in children suffering from falciparum malaria have established elsewhere that all proposed drug combinations are efficacious and safe in East Africa. Extrapolating from trials in children to pregnant women is not, however, reliable either for efficacy (because of differences in pharmacokinetics and immunity) or for side-effects and effect on birth outcome. The relative efficacy and safety of these combinations of drugs during pregnancy are poorly documented. Clinical trials of combinations of antimalarial drugs in pregnant women are urgently needed in order to develop evidence based treatment regimes for malaria during pregnancy.

### **3. OBJECTIVES OF THE STUDY**

The objectives of this study are to assess the therapeutic efficacy and safety of SP as the current first line drug, and three other potential alternative combinations in treating uncomplicated falciparum malaria during pregnancy, in an area with appreciable levels of SP resistance and rising HIV seroprevalence. Specifically the study will compare the clinical and parasitological response to and the side effects of the following drug regimes:

- (a) SP;
- (b) SP + amodiaquine [SPAQ];
- (c) Chlorproguanil+dapsone (Lapdap);
- (d) Amodiaquine + artesunate [AQAS]

### **4. TRIAL DESIGN**

#### **4.1 Primary end point**

The primary end-point of the trial will be treatment failure by day 28. This will be defined as:-

*Any of:-*

- 1) a need for rescue treatment due to clinical deterioration defined by altered sensorium, convulsions, persistent vomiting, renal impairment, respiratory distress, a fall in Hb below 7g/dl, or in cases where initial haemoglobin was less than 9 g/dl a drop of 20% from the starting Hb, at any time during admission;
- 2) persistence of fever with parasitaemia on day 3;
- 3) increasing parasite load on day 3;
- 4) failure to clear parasites on day 7;
- 5) rescue medication for recurrent malaria before day 28;
- 6) slide parasite positivity at day 28.

## **4.2 Secondary endpoints**

Secondary endpoints will include the following:-

1. Incidence of foetal death during treatment, defined as absence of foetal heartbeat assessed by Doppler;
2. Hypoglycaemia requiring treatment;
3. Parasite recrudescence or re-infection on day 14;
4. Parasite clearance on day 3;
5. Level of recovery of haemoglobin on day 14;
6. Fever clearance time;
7. Incidence of perinatal and neonatal mortality, assessed 4-6 weeks after due date of delivery;
8. Clinically apparent neonatal abnormality, assessed 4-6 weeks after due date of delivery;
9. Placental malaria
10. Preterm delivery
11. Other adverse events during treatment.

## **4.3 The trial**

1. This will be a randomized controlled trial with four arms;
2. The slide reader assessing the primary endpoint will be blind to treatment allocation, and analysis will be performed by intention-to-treat;
3. Direct Observed Therapy (DOT) of all doses of study regimens will be employed;
4. Drug doses packed in blister packs, labelled with the patient number will be used where possible.

## **5. SELECTION AND WITHDRAWAL OF PATIENTS**

Pregnant women with mild-moderate, slide proven, falciparum malaria will be recruited from the Antenatal wing (ANC) of the Maternal and Child Health (MCH) clinic at Muheza (Teule) Hospital. Pregnant women from Muheza Township and surrounding villages attend this clinic. Nurses attending the clinic will interview all febrile women and women with a recent (past 24 hours) history of fever and those with a probable diagnosis of malaria will be referred to the study team. Those with signs/symptoms of mild-moderate anaemia will also be referred. All referrals will be re-interviewed and examined by the Medical Officer of the study team to exclude concomitant infection(s). Duplicate thick and thin blood smears will be made, Giemsa stained at pH 7.2, and examined microscopically. The consent form will be administered to those meeting the inclusion criteria and they will be enrolled upon consenting.

### **5.2 Inclusion criteria**

A pregnant woman who has:-

*either* a positive blood smear for *P.falciparum* with at least 1000 asexual parasites/ $\mu$ L in an asymptomatic woman  
*or* any of the following symptoms within 2 days prior to consultation: history of fever; headache, vomiting, chills/rigors, and/or any of the following signs: temperature  $\geq 37.5^{\circ}\text{C}$  and  $< 39.5^{\circ}\text{C}$ , Hb  $\geq 5$  and  $< 9$  g/dl) together with *P.falciparum* parasitaemia at any density

and (in both cases) the following:

1. has no exclusion criterion (see below);
2. is 14-34 weeks pregnant on the day of attending the ANC clinic or OPD;
3. has a viable foetus, defined by presence of foetal heartbeat by sonicaid or pinnard (foetal heartbeat is not heard until 14 weeks);
4. is able to take study drugs by the oral route;
5. is able to attend stipulated days for follow up clinic and provide specimens;
6. gives informed written or witnessed verbal consent to participate by herself, and also through her parent/guardian if aged  $< 15$  years (in conformity to Tanzania Law).

Those  $> 34$  weeks are excluded because they are close to term and may deliver during the 28 day f/u period.

### 5.3 Exclusion criteria

Exclusion criteria include:-

1. severe and complicated forms of malaria (as defined by WHO);
2. pregnancy in the first trimester;
3. a mixed plasmodial infection;
4. complicated pregnancy e.g. signs/symptoms of toxemia of pregnancy;
5. 2 or more abortions or stillbirths;
6. presence of concomitant disease masking assessment of the response to treatment ;
7. an intake of drugs contraindicated in pregnancy e.g. tetracycline, cotrimoxazole or a macrolide antibiotic;
8. an intake of drugs with effective antimalarial activity within the last 2 weeks\*
9. significantly abnormal baseline haematology (except anaemia) or clinical chemistry parameters e.g. laboratory evidence of renal impairment (serum creatinine  $> 2$  mg/dl) or of hepatitis (alanine aminotransferase ALT  $> 5$  times upper limit of normal);
10. previous participation in the study: Women having a second episode of malaria after completing the 28-day follow up will have details recorded and offered quinine but not be re-enrolled.
11. multiple gestation pregnancies eg twins
12. mother aged 38 years or above

Patients with malaria who do not enter the trial because they fulfil an exclusion criterion will be treated in the optimum way decided by the attending physician. In general, those with severe disease will receive parenteral quinine whilst those with mild disease will receive SP.

### 5.4 Withdrawal criteria

Withdrawal criteria will include:-

---

\* prior chloroquine ingestion will not be an exclusion criterion. Drug ingestion in the previous 2 weeks will be ascertained by patient interview as full testing for all locally available drugs with antimalarial activity is not feasible.

1. withdrawal of consent or non-compliance with assigned study regimen;
2. appearance of other species of *Plasmodium*;
3. vomiting within one hour after re-dosing;
4. protocol violation.

If it is necessary to withdraw a patient during the treatment phase, administration of the study drug will be discontinued. If the patient is still parasitaemic, quinine will be given as a rescue therapy unless there are clinical reasons to use another drug. For withdrawals outside the treatment phase the team will carry out all the safety and efficacy assessment measurements that would have been carried out at the next scheduled visit and the same will apply at delivery (unless the patient is lost to follow up). In such cases the study conclusion page in the Clinical Report Form will be completed and the study medication records updated. Patients withdrawn from the study will continue attending routine antenatal care provided by the MCH clinic. Finger prick blood smear for microscopy and Hb. will be done at every withdrawal. If rescue treatment is given, the blood smear will be checked again on day 7 post-treatment to ascertain parasitological clearance. Patients withdrawn before day 7 and not classified as treatment failures will be replaced.

5) Patients who fail on treatment will be treated with rescue treatment and counted as treatment failures (see above).

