## **6.3 Clinical treatment and investigations.**

All women enrolled will be admitted to the research ward (to be built by the GMP) for the first three days for DOT and to monitor clinical response and adverse events. Drugs will be administered by nurses employed by the project. After each administration, the patient will be observed for 45-60 minutes to ascertain drug retention. The dose will be repeated if vomiting occurs within the observation period, and any further vomiting will cause withdrawal from the study and treatment with parenteral quinine. Patients will be treated for symptoms by standard treatment e.g. paracetamol for fever. Women will also continue to receive routine antenatal medicaments of iron supplements, folic acid, and Tetanus Toxoid (TT) given by the MCH. Drugs with an antimalarial activity will not be permitted; if these are essential, the subject will be withdrawn.

Vital signs (temperature, pulse) will be monitored eight hourly during the treatment period and once daily during the remaining period of hospitalisation. Blood pressure will be measured once daily during hospitalisation. Patients will be interviewed using a “clinical assessment form” check list which includes: weakness, chills/rigors, headache, myalgia, dizziness, abdominal pain, anorexia, nausea, vomiting, diarrhoea, palpitations, insomnia, pruritus, coughing, and tinnitus. Blood glucose will be measured on admission and regularly through treatment by glucose stix testing.

Foetal viability (presence of foetal heartbeat) will be monitored daily during admission using a Doppler machine, and at each follow-up visit.

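### Section 5.4 replaces randomised women withdrawn before day 7 for reasons the regimen can cause, and no section fixes their primary-endpoint outcome

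*Protocol*

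**What the plan says.** Section 5.4 lists the grounds for withdrawal: consent withdrawn or non-compliance, appearance of another *Plasmodium* species, "vomiting within one hour after re-dosing", and protocol violation. It then says: "Patients withdrawn before day 7 and not classified as treatment failures will be replaced". Failures are dealt with separately: "Patients who fail on treatment will be treated with rescue treatment and counted as treatment failures". For withdrawal during treatment, study drug stops and "If the patient is still parasitaemic, quinine will be given as a rescue therapy", unless there is a clinical reason to use another drug. A smear and Hb are taken at withdrawal and, after rescue, one more smear on day 7 post-treatment. No day-28 slide is specified for these women.

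Section 6.3 repeats a dose vomited during the 45-60 minute observation period, after which "any further vomiting will cause withdrawal from the study and treatment with parenteral quinine". Appendix 2 repeats this rule. Section 6.4 records intolerance leading to rescue as an adverse event, under a heading that sets such events apart from treatment failure.

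In section 4.1, item 1 of the primary endpoint counts "a need for rescue treatment due to clinical deterioration defined by altered sensorium, convulsions, persistent vomiting" and other listed signs. Item 5 counts only "rescue medication for recurrent malaria before day 28".

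On analysis, section 4.3 says "analysis will be performed by intention-to-treat". Section 11 bases the primary analysis on women who took one or more doses, and a secondary intention-to-treat analysis on all women entered and numbered in the log.

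**The concern.** Non-compliance and repeat vomiting happen after randomisation, and the assigned regimen can cause both. The only blinding that section 4.3 names is that of the slide reader, so nothing in the text shields a withdrawal decision from knowledge of the arm. Replacing a dosed, randomised woman for such a reason does not fit an intention-to-treat analysis unless the plan says that she stays in the denominator and states how she is scored. It does neither expressly.

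The primary endpoint is also unclear for the woman who vomits a dose twice and receives quinine. One reading makes her a failure who is counted and not replaced. The other makes her a withdrawal who is not a failure and is replaced. The choice would be made after her arm is fixed. At stake is the failure rate of regimens that are hard to keep down, which is the quantity that the trial is meant to give policymakers.

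**Working it through.** **Can the text settle how a woman who vomits twice is scored?**

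- *Towards failure:* section 4.1 item 1 names persistent vomiting among the signs of clinical deterioration that need rescue. It does not say whether vomiting a dose and its repeat qualifies.
- *Towards non-failure:* section 5.4 lists her event as a withdrawal criterion, apart from its sentence on failures. Section 6.3 withdraws her. Section 6.4 puts intolerance with rescue outside treatment failure. Section 4.1 item 5 covers rescue for recurrent malaria only.
- *A third text:* Appendix 2 treats any rescue medication as non-cure, but for a day-14 endpoint, which is not the endpoint of section 4.1.

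The text does not settle it.

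**Do her slides settle it?** With only a withdrawal smear and a day-7 smear after rescue specified, item 6 of section 4.1 (the day-28 slide) cannot be assessed from what is required. Section 2 reports that quinine regimens cleared parasitaemia by day 7 in all 200 patients admitted with severe malaria. A slide taken after quinine would therefore tend to credit clearance to the regimen that she vomited.

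**The plan's own figure.** Section 7 (October 2004) gives 72 per arm for 1% against 15%. With two-sided alpha 0.05, 80% power and pooled variance:

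n0 = [1.96 × √(2 × 0.08 × 0.92) + 0.842 × √(0.15 × 0.85 + 0.01 × 0.99)]² / 0.14², which rounds up to 58.

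With continuity correction, n = (n0/4) × [1 + √(1 + 4/(n0 × 0.14))]², which rounds up to 72. The figure reproduces. It does not test this point, but it sets the arm size used below.

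**Size of the effect**

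Inputs:
- Dosing days: one for SP, three for each of the other regimens (section 6.1).
- Failure among women kept: f = 5% in a three-day arm (the best-treatment rate in the original section 7 calculation) and 45% on SP (section 7).
- Chance of vomiting a dose and its repeat on one dosing day: q. The documents give none, so 0.5% to 5% is an assumed range, taken as equal in all arms.

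Formulas: share withdrawn w = 1 − (1 − q)³ for three days and w = q for SP. Risk with withdrawals counted as failures = w + (1 − w)f.

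| q | w, three-day | women of 72 | three-day risk, counted | SP risk, counted | difference |
|---|---|---|---|---|---|
| 0.5% | 1.5% | 1.1 | 6.4% | 45.3% | 38.9 points |
| 2% | 5.9% | 4.2 | 10.6% | 46.1% | 35.5 points |
| 5% | 14.3% | 10.3 | 18.5% | 47.8% | 29.2 points |

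Example at q = 5%: w = 1 − 0.95³ = 0.1426; 0.1426 + 0.8574 × 0.05 = 0.185. With withdrawals excluded, the difference is 45 − 5 = 40 points throughout.

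**Tipping points.** To move 5% to the 10% that the original section 7 calculation treats as equivalent: w = (0.10 − 0.05)/0.95 = 5.3%, or 3.8 of 72 women. To move 1% to 15%: w = (0.15 − 0.01)/0.99 = 14.1%, or 10.2 of 72.

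**In counts.** Suppose an arm reaches 72 after replacing 5 women, so 77 were randomised, and 5 of the 72 fail. Excluding the replaced women gives 5/72 = 6.9% (exact 95% CI 2.3% to 15.5%). Counting them as failures gives 10/77 = 13.0% (6.4% to 22.6%). The estimate nearly doubles. Both intervals include 15%, so the change does not turn an arm that excluded 15% into one that does not.

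**The case against.** The strongest reply is that nothing is lost. Replacement can mean no more than topping up recruitment. Section 11, read literally, keeps a woman who was dosed in its primary population and a woman who was numbered in its intention-to-treat population. Section 5.4 replaces only women not classed as failures, so if repeat vomiting with rescue meets item 1 of section 4.1, she is counted and never replaced.

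Much of this stands, and it limits three inferences that a reader might draw.

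- *That replaced women are dropped from the analysis.* No section says so, and section 11 points the other way.
- *That the withdrawal rule flatly contradicts the primary endpoint.* It is an ambiguity: clinical deterioration with persistent vomiting and vomiting shortly after a re-dose need not be the same event.
- *That the rule favours the three-day regimens generally.* Dosing days differ only between SP and the rest. Among SPAQ, Lapdap and AQAS the direction is unknown. Against SP it assumes similar risk per dose, and sections 6.2 and 7 mention an SP plus placebo group without a placebo schedule; three days of placebo dosing would narrow the gap in exposure. At q = 2% the shift is about 4.5 of 40 points, too small to reverse that comparison.

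The reply does not supply the missing outcome. Keeping a woman in the denominator without a scoring rule, and with only slides taken after quinine, still understates failure. The differing vomiting windows (45-60 minutes in section 6.3, one hour in section 5.4) share an upper limit and matter little.

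**Conclusion.** The point holds as a gap in outcome definition joined to a replacement rule that does not fit section 4.3. The plan does not state the primary-endpoint outcome of women withdrawn before day 7 with rescue, and its sections support two opposite classifications. Under the assumed range for q and f = 5%, the choice moves a three-day arm's failure rate from 5% to between 6.4% and 18.5%, and about four women in an arm of 72 are enough to take 5% to 10%. The true size is unknown because the documents give no vomiting rate; at the low end about one woman per arm is affected. The ambiguity itself rests on no assumption.

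**What to change.** 1. In section 5.4, state that replacement, if kept, only tops up recruitment. Every randomised woman stays in the intention-to-treat denominator, and every dosed woman in the section 11 primary population, in her allocated arm.
2. In section 4.1, state how withdrawal before day 7 with rescue antimalarial is classified for analysis: failure in the primary analysis, exclusion as a sensitivity analysis.
3. Assess withdrawn women who still consent at the day-28 visit.
4. Report withdrawals by arm and reason.
5. Reconcile sections 4.1, 4.3, 5.4, 6.3, 6.4 and 11. This includes which population is primary (sections 4.3 and 11 differ), the vomiting windows, and quinine, which depends on parasitaemia in section 5.4 but not after repeat vomiting in section 6.3. Which clinical rule is right is for the investigators.

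Cost: mostly wording, day-28 follow-up of a few women, and somewhat higher reported failure rates.
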